### Data management

The completed questionnaires are entered into a secure research database, using a web-based data entry system, accessible for research group only. Each patient is assigned a unique study code and this code will be used as a unique identifier in the database to ensure patient anonymity. The list of study codes and the list of eligible participants will be stored separately in a secure file to which only the TC coordinators have access. In study arm 3, a DCO will handle this process.

Data monitoring and quality checks will be undertaken by a team member with vast experience of database management. To make data collection procedures uniform, TCs and the DCO have been provided with thorough training; regular visits will be made by the project coordinator and regular quality assurance sessions will be organised for TCs and DCO.

Owing to the nature of the intervention and the study design, it is not possible to blind the participants but TCs in charge of carrying out the intervention and data collection are not involved in the preparation of the intervention design or in the statistical analyses.

### Proposed sample size

Based on the primary outcome, we target an improved patient empowerment score of 5.25 points on a scale from 15 to 75 (ie, 0.5 SD).^29^ For two-sided tests with alpha=0.05 and power=80%, 63 patients are needed in each arm of the RCT. In order to compensate for a potential 10% dropout rate, 70 patients will be included in each arm. Given that the two paediatric diabetes outpatient clinics together have about 100 patients in each age cohort of adolescents, and considering a 70% participation rate, a 24-month recruitment period is needed to enrol 140 patients in study arm 1 and 2.

### Data analysis

The primary endpoint (total score of the level of empowerment at T2) will be analysed using Fisher’s non-parametric permutation test unadjusted between the intervention group and the control group in the RCT on the Full Analysis Set with imputation of missing values using stochastic imputation. A sensitivity analysis will be conducted with analysis of covariance (ANCOVA) adjusting for stratification variables without imputation. If confounders are found, complementary analyses will be conducted using ANCOVA between the two groups adjusted for these confounders. A confounder is a baseline variable that differs between the groups and influences the primary outcome variable. For comparison between the two randomised groups, Fisher’s non-parametric permutation test will be used for continuous variables, Fisher’s exact test for dichotomous variables, Mantel-Haenszel X^2^ test for ordered categorical variables and Pearson X^2^ test for non-ordered categorical variables. Missing data will be handled with stochastic imputation. Mean difference between the two groups with 95% CI will be presented for all continuous and dichotomous variables. For comparison within groups, Fisher’s non-parametric permutation test for paired observation will be used for continuous variables and Sign test for dichotomous variables and ordered categorical variables.

All analyses will be predefined in a detailed statistical analysis plan before data base lock. In a later stage, a comparison between the intervention group and a youth clinic group (study arm 3) will also be performed. All significance tests will be two sided and conducted at the 5% significance level.

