At both RCT centres, participants are assigned to either the intervention or the control group. This is done with a web-based randomisation system (1:1) employing stratified block randomisation with a random variable block size. Block randomisation ensures that the TCs in the two centres have relatively continuous exposure to the intervention over time, allowing them to keep their skills up to date and to ensure the fidelity of the intervention. The fact that the block sizes vary randomly minimises the possibility of the TCs being able to predict group assignments. Stratification is made by the centre to achieve an equal distribution of patients in the intervention, with control groups at both centres. Furthermore, stratification for sex and glycated haemoglobin (HbA1c) is crucial to ensure the distribution in the groups due to the knowledge that female adolescents have poorer glycaemic control compared with males, and that adolescents with unsatisfactory glycaemic control are a high-risk population.^20 21^ The grouping for HbA1c is based on ISPAD (International Society for Pediatric and Adolescent Diabetes) guidelines 2014.^20^ Overall, this approach decreases the within-centre variability and reduces the risk of bias and confounding.^22^An intention-to-treat principle will be used.

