### Secondary outcome measures

The secondary outcome variables chosen are other important developmental tasks in adolescence and emerging adulthood and in relation to T1D. When evaluating interventions aimed at improving the outcome of young adults with T1D, some recommended core outcomes are set.^30^ These eight outcomes are: measures of diabetes-related burden or stress, diabetes-related quality of life (QoL), number of severe hypoglycaemic events, self-management behaviour; number of instances of diabetic ketoacidosis (DKA), objectively measured HbA1C, level of clinic engagement and perceived level of control over diabetes. In addition, we measure indicators for successful transition and transfer outcomes as proposed by Coyne *et al*,^31^ which include clinic attendance, hospitalisation rates, disease-specific outcomes and transfer-specific satisfaction. See table 1 for an overview of included variables and measurements. Secondary outcomes include endpoint at T2 and change from baseline to T2 (also empowerment), while the subscales in questionnaires will be included in exploratory analyses.

**Table 1 T1:** Overview of variables and measurements in Stepstones-DIAB

Variables/indicators	Measurement	Time point	Source

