**Primary outcome**			
Patient empowerment	Gothenburg Young Persons Empowerment scale (DIAB)^29^	T0, T1, T2	A

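### The unadjusted primary test leaves out the baseline empowerment score and the randomisation strata: valid and powered as planned, but less efficient than a pre-specified ANCOVA

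*Protocol article*

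**What the plan says.** All references are to the protocol article.

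- **Primary test.** Data analysis states that the T2 total score "will be analysed using Fisher’s non-parametric permutation test unadjusted between the intervention group and the control group in the RCT". Missing values are to be filled by stochastic imputation, and the population is the Full Analysis Set. The method is fixed here; it is not left to the later statistical analysis plan.
- **Randomisation.** Participants and recruitment describes 1:1 stratified block randomisation by centre, and adds: "Furthermore, stratification for sex and glycated haemoglobin (HbA1c) is crucial to ensure the distribution in the groups".
- **Baseline score.** Table 1 lists GYPES at T0, T1 and T2. Data collection says that T0 data are obtained before any intervention starts.
- **Where the strata are used.** "A sensitivity analysis will be conducted with analysis of covariance (ANCOVA) adjusting for stratification variables without imputation". Baseline GYPES is not named in that model.
- **Where baseline GYPES is used.** Secondary outcome measures makes change from baseline to T2 a secondary outcome, for empowerment too. Data analysis also allows a complementary ANCOVA on any baseline variable that differs between arms and influences the primary outcome.

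**The concern.** A patient's own T0 score is likely to be among the better predictors of the same score at T2, and it is measured before the intervention. Leaving it out keeps variance in the comparison that a pre-specified covariate would remove, so the confidence interval is wider and power lower than the same patients could give.

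The strata raise a second, smaller point. A permutation across the whole sample is not the reference set that stratified randomisation produced. If the strata predict GYPES, the unadjusted test is conservative.

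The two places where baseline GYPES may appear do not make up for this. The change score is a secondary analysis, and the complementary ANCOVA depends on an imbalance seen in the data. The margin is limited: the design aims at 80% power, and recruiting 140 patients from two clinics is expected to take 24 months.

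**Working it through.** **Inputs from Proposed sample size.** The target difference is 5.25 points, stated as 0.5 SD, so SD = 5.25/0.5 = 10.5. The evaluable number is given as follows: "For two-sided tests with alpha=0.05 and power=80%, 63 patients are needed in each arm of the RCT". The allowance for loss to follow-up is then added: "In order to compensate for a potential 10% dropout rate, 70 patients will be included in each arm".

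**Input not in the article.** The correlation r between the T0 and T2 scores. It is varied from 0.2 to 0.6 below, as an assumption.

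**Step 1: the plan's own figures.** By the normal approximation, n per arm = 2(1.96 + 0.8416)²/0.5² = 62.8, rounded up to 63, and 63/0.90 = 70. Both agree with the article. Power at 63 per arm is Φ(0.5/√(2/63) − 1.96) = Φ(0.846) = 80.1%. The noncentral t distribution gives 79.5%. The 95% CI half-width is 1.96 × 10.5 × √(2/63) = 3.67 points.

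**Step 2: adjusting for T0 GYPES.** The residual SD is 10.5 × √(1 − r²). For 63 per arm:

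| Assumed r | Residual SD | Power | Gain over 80.1% (points) | n per arm for 80% |
|---|---|---|---|---|
| 0.2 | 10.29 | 81.7% | 1.6 | 61 |
| 0.3 | 10.02 | 83.7% | 3.6 | 58 |
| 0.4 | 9.62 | 86.5% | 6.3 | 53 |
| 0.5 | 9.09 | 90.0% | 9.9 | 48 |
| 0.6 | 8.40 | 93.9% | 13.8 | 41 |

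At r = 0.5 the CI half-width falls to 3.67 × 0.866 = 3.18 points. The noncentral t gives nearly the same gains (1.6 points at r = 0.2, 14.1 at r = 0.6). With 70 per arm fully observed, power is 84.1% unadjusted, against 85.5% (r = 0.2) to 95.9% (r = 0.6).

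A simulation with 1,500 runs per value of r gave 78% to 79% for the unadjusted permutation test at every r. ANCOVA gave 82.6% at r = 0.3, 88.4% at r = 0.5 and 94.2% at r = 0.6.

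**Step 3: adjusting for the strata alone.** The share of GYPES variance that they explain (R²) is also not in the article. Replacing r² by an assumed R² of 2%, 5% or 10% gives 80.9%, 82.1% or 84.1% power. The gains in Step 2 therefore come from the baseline score; the strata are not part of that calculation.

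**Step 4: type I error when the strata are ignored.** With exact balance within strata, true alpha = 2(1 − Φ(1.96/√(1 − R²))). At R² = 10% this is 2(1 − Φ(2.066)) = 3.9%. A simulation with eight strata, near-exact balance and a t test standing in for the permutation test gave 4.1%. The departure is towards caution.

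**Step 5: the change score as a substitute.** If the SD is equal at T0 and T2, a change score has SD 10.5 × √(2(1 − r)). This exceeds 10.5 whenever r is below 0.5, and it is never below the ANCOVA residual SD. The secondary change analysis therefore does not recover what the primary test leaves out.

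**The case against.** The strongest reply is that nothing here is wrong. The sample size is for an unadjusted two-group comparison, the primary analysis is one, and the planned power is delivered. A permutation test on a score bounded at 15 and 75 is a legitimate pre-specified choice that avoids model assumptions. That stands, and it makes the point one of efficiency.

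A reader might go further and infer that the trial is underpowered, or that the test is invalid because it ignores the stratification. The article supports neither. Its 63 and 70 per arm reproduce, and any effect of ignoring the strata lowers the false-positive rate.

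A reader might also take a definite loss of, say, 4 to 14 points as established, and put part of it down to the strata. No r is given, so any figure is conditional. At r = 0.2 the gain is under 2 points, and the calculation uses baseline alone. The article justifies stratifying on sex and HbA1c by glycaemic control and risk, not by empowerment, so nothing shows that they explain 10% of GYPES variance. With dropout and incomplete blocks, the conservatism would also be weaker than the formula says.

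Finally, the omitted variables are not absent from the plan. The strata are in the sensitivity ANCOVA, and baseline GYPES has two routes in. These are partial answers: the sensitivity model omits baseline GYPES, and the complementary model chooses its covariates by observed imbalance.

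**Conclusion.** The point holds as a matter of efficiency. The primary test omits the baseline score and the strata, and no stated primary or sensitivity analysis is certain to condition on baseline GYPES. With SD 10.5, a true difference of 5.25 points and 63 evaluable per arm, baseline ANCOVA would raise power from about 80% to between 82% (r = 0.2) and 94% (r = 0.6). The reading of the text is secure; the size is conditional on r. The contribution of the strata is small unless they explain a substantial share of GYPES variance. If they did explain 10%, the unadjusted test would be mildly conservative, with a true alpha of about 4%. It is worth acting on because the gain needs no patients, and it would be a buffer if dropout exceeded 10% or the effect fell short of 5.25 points.

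**What to change.** Before database lock, and without sight of outcome data by arm, pre-specify as primary an ANCOVA of T2 GYPES on arm, T0 GYPES, centre, sex and HbA1c stratum. Report the adjusted mean difference with its 95% CI. If a permutation p-value is preferred, permute within the randomisation strata on the covariate-adjusted statistic, which also avoids reliance on the linear model's distributional assumptions. Keep the unadjusted permutation test as the sensitivity analysis. Fixing these covariates in advance also reduces the need to choose adjustment variables by observed imbalance.

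The change needs no new data and no extra patients. The detailed statistical analysis plan, which the article promises before database lock, is the natural place for it. The cost is more than wording: the primary method is published, recruitment began in August 2019, and participants and transition coordinators are unblinded. The change therefore needs a dated, justified amendment that records that no outcome data by arm had been seen.

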### Patient and public involvement

During the planning phase of this study, young persons from the Swedish patient organisation, ‘Young Diabetes’, have been involved as advisors in the development of certain parts of the intervention. Insufficient transitional care has been on their agenda for several years and the initiative to evaluate support for transition and transfer is therefore highly sought after. Representatives from Young Diabetes will continuously be involved as a reference group during the entire study to secure consideration of young peoples’ priorities, experiences and preferences in all phases. These representatives also participate in the event ‘Adolescent Day’. There is an established advisory board in STEPSTONES that has been involved in the development of the intervention, also including young persons with CHD and parent representatives.^16^ Henceforth, this advisory board will serve the entire STEPSTONES project, and thus young persons with diabetes have been included in the advisory board. Further, this group includes experts on adolescent health and medicine, as well as on the research and implementation of PCC.

### Trial duration

Recruitment of participants began in August 2019 and is expected to be completed in August 2021. Data collection is planned to be completed in January 2024. When data collection is completed, the dataset will be closed and the analysis of data and the dissemination of the results will begin.

### Ethical considerations

For this study, Ethics approval has been obtained from the Regional Ethics Review Board in Stockholm (Dnr 2018/1725-31). A multicentre ethical application includes mandatory approvals from the head of the department at each participating centre.

Before inclusion, an information pack is given to the adolescents and their parents to explain the purpose of the study, its voluntary nature, the right to cease participation at any time, the data storage procedure, and the strict anonymous processing of data. Patients will only be included if the adolescent, who is a minor at the time of inclusion and the parents/guardians provide written informed consent.

The risk of participating in this study is low, as the intervention is supportive in nature. If the transition programme is shown to be effective, the benefits may be substantial. We consider the participants to be vulnerable persons. For some participants, filling out the questionnaires may bring up some unpleasant memories and/or feelings, so contact details of the TCs/DCOs, as well as organisations which can help them cope with these feelings, will be provided in the information pack. Participants are covered by Swedish patient insurance in case of adverse events (AEs).

### Follow-up on AEs

All AEs will be reported within a week to the principal investigator and the project manager. In case of a serious AE, the report will be made immediately. Appropriate measures will be undertaken in every AE to ensure patent safety.

### Dissemination

The results from this study will be published in peer-reviewed journals and will follow the recommendations of the Consolidated Standards of Reporting Trials statement.^40^ Further, abstracts for poster and oral presentation will be submitted to national and international conferences and findings communicated and discussed with healthcare and patient representatives for potential implementation.

## Discussion

This study relies on the experiences from two previous research projects aiming to promote the transition process for youths. The first instance was for adolescents with rheumatoid arthritis, the second is the current STEPSTONES-CHD research project by testing a further developed transition programme in adolescents with CHD,^16 41^ and now we are expanding to evaluate the effectiveness of a structured, person-centred transition programme for adolescents with T1D. The focus is to increase their level of empowerment in order to promote their ability to navigate through the adult care system, participate in care planning, and increase self-management and decision-making skills.^6 7^

As previously stated, creating effective clinical processes for the transition from paediatric to adult care is particularly important in order to optimise well-being and health in emerging adults with T1D. This includes achieving target glycaemic control to prevent long-term complications and to maximise lifelong functioning. Although there is a lack of proven strategies to achieve these goals, programmes that particularly target adolescents with T1D through education, skills training, special transition clinics and/or addition of TCs appear to be promising.^10 42^However, the current knowledge regarding this transition process calls for ongoing and expanding research initiatives in order to determine the effectiveness of transition programmes for adolescents with different long-term conditions.^9 43^

One of the strengths of this study is the chosen design; employing an RCT is considered the gold standard when evaluating the effectiveness of interventions and provides the highest level of evidence. By using stratiﬁed block randomisation, we ensure that the intervention and control groups are balanced in terms of potential confounding factors, for example, equal distribution, thereby minimising the risk of biasing the result. In a previous empowerment-based study including a person-centred group education for youths with T1D, the results highlighted the importance of an approach that strengthens young people’s independence and autonomy. The parents’ attitude was also highlighted in this process. The adolescents described the importance of a permissive atmosphere and that it was perceived as positive to meet at new healthcare professional in these encounters. Moreover, the adolescents said it was empowering to meet others with T1D.^44^ For HbA1c, an effect could only be seen for boys.^45^ Another strength is that projects can use the lessons learnt from STEPSTONES-CHD in terms of feasibility and fidelity. For example, experiences of SOPs for recruitment and data collection will secure data entry. Moreover, in the training of the TCs, the experienced TCs from STEPSTONES-CHD could be used as tutors and mentors, which further secures delivery of the generic intervention components in STEPSTONES-DIAB. By employing experienced diabetes nurses as TCs, we ensure that the generic components are adapted to and relevant for diabetes care. Further, the generic components in the person-centred transition programme, as well as the generic outcome measures, provide opportunities to compare findings across different conditions. If the programme is proven effective, these circumstances may facilitate future implementation of transfer and transition strategies in clinical practice.

A challenge in complex interventions like transition programmes is the multiple interacting components and behaviours required by those delivering and receiving the intervention. To evaluate the full extent of a complex intervention in addition to effectiveness, the evaluation must incorporate process assessments of how the intervention is being delivered in practice and what causal mechanisms lead to the desired outcomes. Based on the experiences from the more extensive process evaluation undertaken in STEPSTONES-CHD,^17^ we have identified certain process evaluation components that also need to be undertaken in STEPSTONES-DIAB in order to promote future implementation. These components reflect what is delivered (fidelity, adherence, dose, reach, acceptability) and are provided through participant observations, the intervention implementation form, enrolment form and transition plans.^17^

Some limitations need to be acknowledged in this study. First, this intervention focuses on preparation for transition to adulthood and the actual transfer to adult care. Additional interventions may be needed to secure continuity of care after transfer. Second, the lack of blinding procedures poses a limitation in that the nature of study makes blinding patients and TCs impossible. Third, the short follow-up period of 6 months at the age of 18.5 years cannot be considered enough to evaluate long-term effects of the transition programme. There is a great need to evaluate such effects^9^ and these must be followed up in separate studies after additional consent and funding.

## Conclusion

The empirical underpinning of the guidelines, recommendations and statements regarding successful transitional strategies is weak and to be considered expert-based rather than evidence based. Based on an RCT design and building on previous projects, STEPSTONES-DIAB has the research capacity to provide high-level evidence within this area, and thereby contribute to filling the gaps in scientific knowledge related to transitional care of adolescents with T1D.
